## Abstract

**Background:**

Initiation of anticoagulation therapy in ischemic stroke patients is contingent on a clinical diagnosis of atrial fibrillation (AF). Results from previous studies suggest thromboembolic risk may predate clinical manifestations of AF. Early identification of this cohort of patients may allow early initiation of anticoagulation and reduce the risk of secondary stroke.

**Objective:**

This study aims to produce a substrate-based predictive model using cardiac magnetic resonance imaging (CMR) and baseline noninvasive electrocardiographic investigations to improve the identification of patients at risk of future thromboembolism.

**Methods:**

CARM-AF is a prospective, multicenter, observational cohort study. Ninety-two patients will be recruited following an embolic stroke of unknown source (ESUS) and undergo atrial CMR followed by insertion of an implantable loop recorder (ILR) as per routine clinical care within 3 months of index stroke. Remote ILR follow-up will be used to allocate patients to a study or control group determined by the presence or absence of AF as defined by ILR monitoring.

**Results:**

Baseline data collection, noninvasive electrocardiographic data analysis, and imaging postprocessing will be performed at the time of enrollment. Primary analysis will be performed following 12 months of continuous ILR monitoring, with interim and delayed analyses performed at 6 months and 2 and 3 years, respectively.

**Conclusion:**

The CARM-AF Study will use atrial structural and electrocardiographic metrics to identify patients with AF, or at high risk of developing AF, who may benefit from early initiation of anticoagulation.

Key Findings
▪Undiagnosed atrial fibrillation is the underlying cause of a significant proportion of strokes originally classified as embolic stroke of unknown source (ESUS).▪Atrial fibrillation is associated with marked structural abnormalities of the left atrium, including dilatation, spherical remodeling, and atrial late gadolinium enhancement, which may be quantified using atrial cardiac magnetic resonance imaging.▪This study will test the hypothesis that identification of these structural abnormalities using atrial cardiac magnetic resonance imaging can identify the subset of ESUS patients at risk of atrial fibrillation using the gold standard of implantable loop recorder monitoring as the comparator.▪A poststroke model assessing atrial substrate predictive of developing atrial fibrillation may allow for earlier detection of patients at thromboembolic risk and allow earlier initiation of anticoagulation in these patients.

## Introduction

Atrial fibrillation (AF) is a major risk factor for ischemic stroke resulting in significant morbidity and mortality, but may not be identified by routine clinical monitoring during post-stroke care.^1^ It is estimated that 25% of embolic strokes of unknown source (ESUS) can be attributed to undiagnosed AF, with the risk of stroke recurrence in this cohort being high following the primary stroke event.^2^^,^^3^ Secondary stroke risk reduction in AF patients can be achieved by timely initiation of anticoagulation therapy.

Current guidelines for initiation of anticoagulation mandate electrocardiographic documentation of AF.^4^ Two landmark trials (EMBRACE and CRYSTAL-AF) provide evidence that increased AF detection rates are possible with prolonged ambulatory monitoring or following insertion of an implantable loop recorder (ILR).^5^^,^^6^ However, median AF detection time in real-world studies ranges from 40 days (interquartile range: 14–84 days) to 112 days (interquartile range: 35–293 days).^5^^,^^7^ With a risk reduction from 12% to 4% per year (hazard ratio 0.34; 95% CI 0.36–0.79) following the use of anticoagulation, delays in initiation of therapy are likely to have an impact on the incidence of secondary stroke.^8^ In addition, a requirement for prolonged monitoring is associated with an increased cost burden and need for further resources to accommodate follow-up.

A further limitation on the requirement of AF documentation is the discordance in temporality, biological gradient, and specificity between AF and ischemic stroke previously reported.^9^, ^10^, ^11^ Both the ASSERT and IMPACT trials enrolled patients with an implantable cardiac device prior to the index stroke event and demonstrated discordance in temporality, with up to 16% of patients in the ASSERT study being diagnosed with AF *after* the index stroke event despite prior device insertion.^9^, ^10^, ^11^ These studies suggest that elevated thromboembolic risk may exist prior to clinical detection of AF. Furthermore, while the ROCKET-AF Trial suggested an increase in adjusted rates of stroke or systemic embolism in the persistent AF group compared with the paroxysmal AF group (OR: 2.18 vs 1.73), the RE-LY Trial found no statistically significant change in thromboembolic risk between groups, suggesting that increased duration of AF may not be associated with increased stroke risk.^12^^,^^13^ In addition, previous meta-analyses have suggested that restoration of sinus rhythm does not reduce the risk of stroke,^14^^,^^15^ providing the underlying basis for continuation of anticoagulation for the purposes of stroke risk reduction regardless of treatment strategy following AF diagnosis if risk factors are present. As such, it is conceivable that patients with short paroxysms of AF who remain at high risk for secondary stroke may be undiagnosed by current standards of poststroke investigation of AF, which often include an electrocardiogram (ECG) and 24-hour Holter monitor. Combined, these studies suggest that elevated thromboembolic risk may exist prior to clinical detection of AF and represent a further delay in initiation of anticoagulation therapy in a high-risk cohort.

Previous ESUS studies, including NAVIGATE-ESUS and RESPECT-ESUS, have unsuccessfully attempted to identify this cohort for early initiation of anticoagulation.^16^^,^^17^ Recent models suggest comorbidities associated with elevated stroke risk (eg, hypertension, diabetes, vascular disease) and known to be associated with atrial disease may provide an atrial thromboembolic substrate even prior to the development of clinical arrhythmia.^9^^,^^18^

*A poststroke model assessing atrial substrate predictive of developing AF may allow for earlier detection of patients at thromboembolic risk, allowing for earlier initiation of anticoagulation.*

A novel term, “atrial cardiomyopathy,” has been described that refers to atrial remodeling resulting in “clinically relevant structural and electrophysiological changes of the atrium.”^19^ Atrial fibrosis plays a central role in the AF substrate, having been identified histologically in patients with AF and in patients with risk factors for AF. Atrial geometry also plays an important role in the pathogenesis of AF, with left atrial enlargement being greater in patients with persistent vs paroxysmal AF and atrial sphericity more pronounced in those with recurrent AF.^20^ In patients with AF, increasing atrial late gadolinium enhancement (LGE) on cardiac magnetic resonance (CMR) imaging is associated with increased risk of major adverse cardiovascular and cerebrovascular events, driven primarily by an increased risk of stroke or transient ischemic attack.^21^ Although atrial CMR imaging has frequently been used for substrate assessment in patients with known AF, few studies have published data regarding atrial substrate assessment in ESUS patients, highlighting a key knowledge gap.^22^ Identifying ESUS patients displaying these structural changes in the absence of AF may arguably identify patients at higher risk of developing AF and who may benefit from early anticoagulation poststroke.

Similarly, electrophysiological changes present on surface ECG have previously been highlighted in the literature as indirect surrogate markers of atrial cardiomyopathy and stroke. Analyses of p waves from the surface ECG show that p-wave terminal force in lead V_1_ (PTFV_1_) is independently associated with stroke, as well as structural atrial disease including atrial dilatation and fibrosis.^23^^,^^24^ Both PTFV_1_ and supraventricular ectopy have also previously been shown to be strong predictors of paroxysmal AF in ischemic stroke patients.^25^^,^^26^

Taken together, these observations suggest that left atrial structural and electrical remodeling are associated with stroke and predictive of the presence of paroxysmal AF even in the absence of documented AF at the time of the index stroke.

The CARM-AF study therefore seeks to detect atrial remodeling in a subset of patients with prior ischemic stroke and no AF detected during routine assessment. We hypothesize that the degree of structural and electrical remodeling present at the time of the first stroke will be predictive of the subsequent occurrence of AF as documented by gold-standard long-term ILR monitoring. The results of CARM-AF can inform future randomized controlled trials where clinical decisions regarding anticoagulation therapy are made at the time of the index stroke, potentially reducing the risk of secondary stroke.

## Objectives

The overall research aim is to produce a substrate-based predictive model using CMR and electrocardiographic parameters that may better identify ESUS patients at risk of developing AF.

The principal research question is to determine if atrial CMR imaging can predict the occurrence of AF in advance of the clinical arrhythmia in patients with confirmed ischemic stroke. The specific hypotheses that will be tested are as follows: (1) left atrial LGE in patients with ESUS is greater in patients with AF than those without AF documented by ILR; and (2) left atrial sphericity in patients with ESUS is greater in those patients with AF than those without AF documented by ILR.

The secondary research question is to determine whether electrocardiographic parameters can predict the occurrence of AF in advance of the clinical arrhythmia in patients with confirmed ischemic stroke. The specific hypotheses that will be tested are as follows: (3) PTFV_1_ in patients with ESUS is greater in those patients with AF than those without AF documented by ILR; and (4) supraventricular ectopy in patients with ESUS is greater in those patients with AF than those without AF documented by ILR.

As described in Data Analysis, below, further analysis will be performed to combine structural and electrical variables into a single score to improve prediction of AF status, which can be employed in future randomized controlled trials.

## Design

The CARM-AF Study is a multicenter, prospective, observational study of patients who have been diagnosed with an embolic stroke of unknown source in the absence of documented atrial fibrillation. The study conforms to the principles outlined in the Declaration of Helsinki. Ethical approval has been granted by Health Research Authorities and the South London Research Ethics Committee (REC: 19/LO/1933). The study is funded by the British Heart Foundation (PG/19/44/34368).

### Trial design

A total of 92 patients will be recruited to undergo a CMR scan for investigation of features suggestive of left atrial remodeling. This will be followed by implantation of an ILR as standard of care for detection of AF as per the 2021 NICE guidelines.^27^ Remote ILR follow-up will occur at 6 months, 1 year, 2 years, and 3 years as part of this study. Throughout the study period routine follow-up will be conducted by daily telemetric monitoring using the Reveal CareLink system (Medtronic). Patients in whom AF has been detected will be allocated to the study group and patients in whom AF has not been detected will be allocated to the control group (Figure 1). Group allocation will be determined by 2 independent experts.

**Figure 1 fig1:**
[figure not shown]
Trial flowchart. AF = atrial fibrillation; CMR = cardiac magnetic resonance; GSTT = Guy’s and St Thomas’ Hospital; ILR = implantable loop recorder.

### Sample size justification

Previous data suggest that ILR monitoring will identify AF in 25% of ESUS patients with a CHA_2_DS_2_VaSc score of 3.^2^ We anticipate that our study population will have a 3:1 ratio of non-AF and AF patients. This ratio has subsequently been validated in the recent LOOP study.^28^

Pilot data analysis was performed using CEMRGapp, using the image intensity ratio to define atrial fibrosis at image intensity ratio >0.97.^29^ This analysis suggested a population mean difference of 6% in left atrial LGE burden between AF and non-AF patients, with standard deviations of 9% and 4% in the AF and non-AF group, respectively (Figure 2). For estimating the sample size required to detect a difference in LGE burden between stroke patients with and without AF, we allow for unequal variances and assume that cases (AF on ILR monitoring) represent 25% of the study population while controls (no AF on ILR monitoring) represent 75% of the study population. Group sample sizes of 21 and 63 would achieve 80.8% power to reject the null hypothesis of equal means when the population mean difference is μ1 − μ2 = 47.0 − 41.0 = 6.0, with standard deviations of 9.0 for group 1 and 4.0 for group 2, and with a significance level (alpha) of 0.05 using a 2-sided 2-sample unequal-variance *t* test.

**Figure 2 fig2:**
[figure not shown]
Atrial cardiac magnetic resonance (CMR) pilot data in stroke and control patients. Illustration of atrial CMR findings in stroke (n = 8) and control patients (n = 8). **A:** Raw data and processed data appearances. **B:** Late gadolinium enhancement and sphericity quantification illustrating medians, interquartile ranges, and data ranges. IIR = image intensity ratio; LA = left atrium.

For estimating the sample size required to detect a difference in sphericity between stroke patients with and without AF, we again assume cases and controls represent 25% and 75% of the study population, respectively. Group sample sizes of 14 and 42 would achieve 82.5% power to reject the null hypothesis of equal means when the population mean difference is μ1 − μ2 = 80.0 − 77.0 = 3.0, with a standard deviation for both groups of 3.3 and with a significance level (alpha) of 0.05 using a 2-sided 2-sample equal-variance *t* test. Taking the larger of these estimates and allowing for 10% loss to follow-up indicates that a sample size of 92 patients is required for this study. With this sample size, assuming the 3:1 ratio of non-AF to AF individuals we would be able to estimate the area under the curve of a receiver operating characteristic (ROC) curve with 95% confidence interval width (upper-lower confidence limit) of between 0.21 and 0.28 for area-under-the-curve values between 0.85 and 0.65, respectively.

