## Data analysis

Primary analysis will be performed following 12 months of continuous ILR monitoring with interim and delayed analyses performed at 6 months and 2 and 3 years, respectively. Descriptive statistics will be used to characterize the study population. Structural and electrocardiographic metrics will be summarized. Results will be reported as a comparison between the standard deviation and mean difference. If groups show a normal distribution, *t* test will be performed to assess for a significant difference between groups; otherwise, a Mann-Whitney *U* test will be used. The χ^2^ test will be used for categorical data. Any *P* value <.05 will be considered significant. For qualitative assessment of LGE, patients will be categorized as per our routine clinical practice using combined assessment of both LGE methods as none, mild, moderate, or severe LGE. Survival analysis will be performed using Kaplan-Meier curves with atrial fibrillation as the outcome measure. For qualitative assessment of atrial LGE, our open-source platform, CEMRGApp, will be used to create LGE scores. ROC analysis will be used to determine if there is a quantitative LGE cut-off with adequate specificity and sensitivity to detect atrial fibrillation during follow-up. To combine these variables into a single score, the use of logistic regression, shallow classifiers, atrial computational modeling, or combining variables using summated z-scores will be explored to improve the predictive value for AF.

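### The AUC precision in the sample size section ignores the unequal LGE standard deviations used to size the trial, and is optimistic for LGE

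*Protocol article*

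**What the plan says.** All the design figures are under Sample size justification in the protocol article.

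- **LGE comparison.** "Group sample sizes of 21 and 63 would achieve 80.8% power", for a "population mean difference is μ1 − μ2 = 47.0 − 41.0 = 6.0", "with standard deviations of 9.0 for group 1 and 4.0 for group 2". Group 1 is AF and group 2 is non-AF. The test is a two-sided unequal-variance t test.
- **Sphericity comparison.** Equal standard deviations of 3.3, a difference of 3.0, and groups of 14 and 42.
- **Total.** The larger requirement is taken, and "allowing for 10% loss to follow-up indicates that a sample size of 92 patients is required for this study".
- **AUC precision.** The section closes, "assuming the 3:1 ratio of non-AF to AF individuals", with a "95% confidence interval width (upper-lower confidence limit) of between 0.21 and 0.28 for area-under-the-curve values between 0.85 and 0.65, respectively". It names no marker, formula or distribution.

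Under Data analysis, "ROC analysis will be used to determine if there is a quantitative LGE cut-off with adequate specificity and sensitivity to detect atrial fibrillation during follow-up". Under Fibrosis assessment, ROC analysis also selects the image intensity ratio used to define LGE. The article names ROC analysis for no other marker.

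**The concern.** One section treats LGE in two ways. The t-test calculation gives the smaller AF group more than twice the spread of the non-AF group. The AUC statement appears to come from a formula into which no standard deviation can be entered. When the smaller group is the more variable one, the estimated AUC is less precise than that formula indicates.

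The study aims at a predictive model to inform a later randomized trial, so a reader will use this sentence to judge how well discrimination will be known. If it does not hold for LGE on the plan's own inputs, the design is credited with precision it does not have for that marker.

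**Working it through.** **Inputs (Sample size justification).** AF : non-AF = 1 : 3. Group sizes m = 21 (AF) and n = 63 (non-AF), 84 in total, or 23 and 69 if all 92 are evaluable. LGE difference 6.0, standard deviations 9.0 and 4.0. Sphericity standard deviation 3.3 in both groups.

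**Common formula.** For AUC = A,

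Var(A) = [A(1−A) + (m−1)(Q1−A²) + (n−1)(Q2−A²)] / (mn), with 95% width = 2 × 1.96 × √Var.

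Here Q1 is the probability that two AF patients both exceed one non-AF patient, and Q2 the probability that one AF patient exceeds two non-AF patients. The calculations differ only in how Q1 and Q2 are obtained.

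**Step 1: reproduce the plan's figures.** Hanley-McNeil sets Q1 = A/(2−A) and Q2 = 2A²/(1+A). At 21/63:

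- A = 0.65: Q1 = 0.4815, Q2 = 0.5121. Var = [0.2275 + 20(0.0590) + 62(0.0896)]/1323 = 0.00526, SE 0.0726, width 0.284.
- A = 0.85: Q1 = 0.7391, Q2 = 0.7811, SE 0.0556, width 0.218.

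At 22/66 the widths are 0.278 and 0.213; at 23/69 they are 0.272 and 0.208. The printed range is reproduced to within 0.01. Both t-test powers also reproduce (80.8% and 82.5%).

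**Step 2: the AUC implied by the LGE inputs.** With normal data, A = Φ(6/√(9² + 4²)) = Φ(6/√97) = 0.729.

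**Step 3: use the LGE standard deviations.** Q1 and Q2 are now computed by numerical integration for normal data with standard deviations 9 (AF) and 4 (non-AF), the mean shift being set to give each A. At A = 0.729 and 21/63:

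- Hanley-McNeil: Q1 = 0.5733, Q2 = 0.6145. Var = [0.198 + 0.843 + 5.167]/1323 = 0.00469, width 0.268.
- Standard deviations 9 and 4: Q1 = 0.5499, Q2 = 0.6522. Var = [0.198 + 0.375 + 7.504]/1323 = 0.00611, SE 0.0781, width 0.306.

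The variance ratio is 8.077/6.208 = 1.30. The increase comes from the Q2 term, which reflects the spread among the few AF patients.

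| AUC | Hanley-McNeil, 21/63 | SD 9 and 4, 21/63 | Hanley-McNeil, 23/69 | SD 9 and 4, 23/69 |
|---|---|---|---|---|
| 0.85 | 0.218 | 0.239 | 0.208 | 0.228 |
| 0.729 | 0.268 | 0.306 | 0.256 | 0.293 |
| 0.65 | 0.284 | 0.332 | 0.272 | 0.317 |

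Simulated DeLong intervals under the same model have mean widths of 0.232 and 0.331 (21/63) and 0.223 and 0.317 (23/69) at AUCs of 0.85 and 0.65.

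**Step 4: position relative to 0.5 at the implied AUC.** Lower limit = 0.729 − 0.306/2 = 0.576 at 21/63, and 0.729 − 0.293/2 = 0.583 at 23/69.

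**Step 5: the equal-SD marker.** With equal standard deviations at 21/63, the widths are 0.187 at AUC 0.85 and 0.270 at AUC 0.65. For sphericity the printed range is slightly too wide.

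**The case against.** - **The figure is generic and correctly computed.** This stands. The sentence names no marker, and the plan also foresees a combined score whose variance pattern is unknown. A reader might infer an arithmetic error; Step 1 shows there is none. But LGE is the marker for which ROC analysis is named, and the preceding calculation states its variance pattern.
- **The standard deviations are weak inputs.** This stands in part. They are pilot values at one intensity-ratio threshold, and the final threshold is to be chosen by ROC analysis. Figure 2 describes 8 stroke and 8 control patients. If the standard deviations came from groups of 8 (an assumption) with normal data, the 95% interval for their ratio would run from about 1 to 5. At a ratio of 1 the printed range is not optimistic. Still, the trial is sized on these same values.
- **Normality is assumed.** It is: Data analysis provides for a Mann-Whitney test if normality fails. The t-test power calculation makes the same assumption.
- **Loss of significance at AUC 0.65.** A reader might infer that an LGE AUC of 0.65 would no longer be distinguishable from chance. The document does not support this as a finding. It never promises to exclude 0.5, and an AUC of 0.65 corresponds to a difference of about 3.8 points, not the planned 6. The crossing is also thin: the lower limit moves from 0.508 to 0.484 at 21/63, a parametric binormal interval at 23/69 gives 0.503, and a logit-scale Hanley-McNeil interval at 21/63 already gives 0.498.
- **Coverage of the reported interval.** A reader might infer that the final intervals will under-cover. The article names no interval method for the analysis, and that choice can properly sit in the analysis plan.
- **Nothing is decided by this sentence.** True. The total of 92 comes from the LGE t test, and no success criterion uses the AUC width. This limits the importance of the point but does not make the figure right for LGE.

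**Conclusion.** The point holds as an inconsistency of assumptions within one section. On the plan's own LGE inputs the stated precision is optimistic throughout the AUC range: by about 0.02 in width at AUC 0.85, 0.04 at 0.73 and 0.05 at 0.65. The most telling case is the AUC implied by the planned difference, where the width exceeds the stated maximum whether 84 or 92 patients are evaluable. The consequence is lower precision for LGE discrimination, not loss of the expected signal.

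The size rests on normally distributed LGE and on the 9 : 4 ratio of standard deviations holding at every AUC. Neither the power calculations nor the sample size is affected.

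**What to change.** Reword the precision sentence under Sample size justification:

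1. For LGE, state a 95% width of about 0.24 to 0.33 for AUCs of 0.85 to 0.65 with 84 evaluable patients (about 0.23 to 0.32 with all 92), computed with standard deviations of 9 and 4. Say that normality is assumed and that the standard deviations come from pilot data.
2. Keep 0.21 to 0.28 only as a generic approximation, with its method named, and note that it is slightly conservative for an equal-SD marker such as sphericity (about 0.19 to 0.27 with 84).

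The cost is a sentence or two of text, with no extra patients or data. The drawback is a less favourable precision statement for LGE. No claim about excluding 0.5 at AUC 0.65, or about interval coverage, needs to be added.
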